### Statistical analysis

Sample size was determined prospectively as described in a previous study that used similar outcome measurements [21]. The following formula was used to estimate sample size [26]:

A previous study reported [21] an improvement of 18.0 in the main outcome NDI index score after treatment with 50 mg itopride. In this study, we anticipate an improvement of no less than 15.0 after acupuncture treatment; however, there are no previous data regarding NDI scores for the treatment of FD using acupuncture. Accordingly, an improvement of 3.0 in the NDI scores of two groups will be considered minimally significant. Standard deviation was defined as 22.0, according to the previous study [21]. Calculations were performed using 90% power and a 5% significance level, resulting in an estimated 120 patients per group. Thus, we must enroll 720 patients in the six groups, to allow for a 15% withdrawal rate.

The two-sided null hypotheses to be tested include:

(1) The primary outcomes of the acupoint treatment groups will be equivalent to those of the itopride control group.

(2) The primary outcomes of the acupoint treatment groups will be equivalent to those of the non-acupoint control group.

(3) The primary outcomes of the acupoint treatment groups will be equivalent to each other.

We will test these hypotheses with a significance level of P < 0.05. The first step of the analysis will involve comparing the baseline characteristics of the groups. The second step will be to compare the efficacy of acupoint and itopride in the treatment of FD. The third step will involve comparing the acupoint treatment group with the non-acupoint control group. If acupoint treatment is more effective than non-acupoint treatment in the treatment of FD, the fourth step will involve comparing the efficacy of four acupoint treatments.

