The analyses of baseline characteristics, as well as the primary, secondary and other outcomes, are based on the intention-to-treat (ITT) principle. Data distribution is expected to be normal owing to the large sample size. However, any skewed distribution data will be transformed prior to analysis. The repeated measures analysis will be used in the assessment of different time points (such as comparing NDI scores before randomization, 2 weeks and 4 weeks after randomization, and 1 month and 3 months after the completion of treatment). Missing values will be addressed using the method of last observation carried forward (LOCF) and multiple-imputation. We will perform sensitivity analysis to determine how these two methods affect the analytic results. General linear mixed models, adjusted for clinical site, will be used to study the effects of treatments on outcomes from baseline to 3 months. Additionally, time-to-event outcomes between groups will be compared using the log-rank test.

Analysis of data will be performed in a blinded manner by a designated statistician at the National Clinical Trial Center of Chinese Medicine (Chengdu GCP Center) in China. Statistical analyses will be performed using SPSS 15.0 statistics software (SPSS Inc, Chicago, Illinois, USA) and SAS 9.0 (SAS Institute Inc., Cary, North Carolina, USA).

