We choose itopride as the drug control because it has been shown to be an effective drug for FD. Furthermore, itopride caused fewer adverse events than did other gastrointestinal prokinetic agents [21]. Therefore, we will attempt to maintain a non-inferiority design because acupuncture is associated with no significant side effects. However, our trial will be limited by our inability to blind patients from knowing whether they are receiving acupuncture or itopride treatment. This factor may cause a high drop-out rate in the itopride group because patients will expect to receive acupuncture treatment when they join the trial. To prevent the expected high drop-out rate, patients in the itopride group will be provided with 10 sessions of free acupuncture after the entire trial has been completed.

Central randomization, a strict and complete form of randomization, will be used in this trial. This method not only provides rapid determination of group assignment, but also ensures adequate allocation concealment. In this trial, we will use transcutaneous electric acupoint stimulation (HANS) to avoid the performance bias generated by acupuncture practitioners. This method will provide accurate electric stimulation to ensure that every patient receives the same level of treatment.

We have devoted much effort to defining the non-acupoint control groups because the locations of non-acupoint treatments will differ from those described in the literature. Most Chinese studies have selected non-acupoints that lie beside the therapeutic acupoint, and halfway between the two lines or two acupoints [24]. However, reports in the Western literature have recorded the location of non-acupoints differently [29,30]. In our previous trial, we designed our two control groups according to the consensus of a panel of acupuncture experts. Thus, the non-acupoint control group in the current study was defined according to the first phase of our ***973 program***.

Briefly, this trial aims to determine if acupuncture is an effective treatment for FD. We will also assess differences in the specific effects of acupoints, as described in traditional theories. Certain procedures described herein, such as the randomization procedure, as controlled by central randomization system, and the standardized protocol for acupuncture manipulation, can be applied to future acupuncture studies.

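### LOCF stands level with multiple imputation and neither is primary, although high drop-out on itopride is anticipated; if itopride patients leave early, LOCF can tilt that comparison toward acupuncture

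*Protocol article*

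**What the plan says.** All references are to the protocol article.

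- **Handling of missing values (Statistical analysis).** "Missing values will be addressed using the method of last observation carried forward (LOCF) and multiple-imputation". The next sentence adds: "We will perform sensitivity analysis to determine how these two methods affect the analytic results". No sentence says which of the two gives the main result.
- **Model (Statistical analysis).** "General linear mixed models, adjusted for clinical site, will be used to study the effects of treatments on outcomes from baseline to 3 months". The text does not say whether this model is fitted to the observed visits or to data already filled in by LOCF or imputation.
- **Analysis population (Statistical analysis).** The analyses "are based on the intention-to-treat (ITT) principle".
- **Drop-out.** The sample-size paragraph makes one allowance for all six groups: "to allow for a 15% withdrawal rate". On the fact that patients know whether they get acupuncture or itopride, the Discussion says: "This factor may cause a high drop-out rate in the itopride group". The reason given is that patients join expecting acupuncture. A countermeasure follows: "To prevent the expected high drop-out rate, patients in the itopride group will be provided with 10 sessions of free acupuncture", given once the whole trial is over.
- **Aim of the itopride comparison.** The Discussion says a non-inferiority design will be attempted. The Statistical analysis section lists two-sided null hypotheses of equivalence.
- **Visits (Table 1).** The NDI and the Symptom Index of Dyspepsia are scored at week 0, weeks 2 and 4, and 1 and 3 months after treatment.

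**The concern.** LOCF gives a patient who leaves the last score on record for every later visit. When scores change over time and drop-out differs between arms, this biases the difference between arms even if leaving has nothing to do with outcome. A mixed model on the observed visits is not biased in that situation.

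The Discussion describes just such a setting: an unblinded arm from which patients may leave because they wanted the other treatment. Drop-out of that kind plausibly comes early. A patient who leaves before week 2 has only the baseline score, so LOCF records no improvement at any visit. If more itopride patients do this, itopride looks worse than it is, and acupuncture passes a non-inferiority comparison more easily.

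With two methods of equal standing and no stated primary, it is also undecided which result counts if they disagree. LOCF further treats filled-in values as if they had been observed, so its standard errors are not right.

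**Working it through.** The plan gives no figure for the effect of LOCF, so there is none to reproduce. The check below does not depend on the sample-size calculation.

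**Inputs from the protocol article (Statistical analysis)**
- Improvement on itopride: "an improvement of 18.0 in the main outcome NDI index score after treatment with 50 mg itopride".
- Anticipated improvement on acupuncture: at least 15.0.
- Smallest difference treated as important: 3.0 NDI points.
- Withdrawal: 15%, not split by arm.

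**Assumptions (not in the documents)**
- Drop-out d_I on itopride and d_A on acupuncture.
- f, the share of a patient's eventual improvement already present at the last observed visit, taken as equal in both arms.
- Patients who leave would otherwise have had their arm's mean improvement.

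**Formula.** With eventual improvement M, the arm mean under LOCF is M × [(1 − d) + d × f], so it falls short by M × d × (1 − f). If both arms truly improve by 18.0, the shift of the difference toward acupuncture is

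18.0 × (d_I − d_A) × (1 − f).

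**Results with d_A = 10%** (positive = toward acupuncture)

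| d_I | f = 0 | f = 0.5 | f = 1 | f = 1.25 |
|---|---|---|---|---|
| 20% | 18 × 0.10 × 1 = 1.8 | 18 × 0.10 × 0.5 = 0.9 | 0 | 18 × 0.10 × (−0.25) = −0.45 |
| 25% | 18 × 0.15 × 1 = 2.7 | 18 × 0.15 × 0.5 = 1.35 | 0 | 18 × 0.15 × (−0.25) = −0.675 |
| 30% | 18 × 0.20 × 1 = 3.6 | 18 × 0.20 × 0.5 = 1.8 | 0 | 18 × 0.20 × (−0.25) = −0.9 |

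f = 0 means leaving before any improvement. f = 1.25 means leaving at a peak 25% above the level that would have been seen later, for example after treatment ends and symptoms partly return.

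**Second setting, with the protocol's own 18.0 and 15.0.** The true difference (acupuncture minus itopride) is −3.0. Take d_A = 15%. The shift is [18.0 × d_I − 15.0 × 0.15] × (1 − f).
- f = 0: d_I = 20% gives 3.60 − 2.25 = 1.35; 30% gives 5.40 − 2.25 = 3.15; 40% gives 7.20 − 2.25 = 4.95. At 30% the LOCF difference is −3.0 + 3.15 = +0.15, so the whole deficit disappears.
- f = 0.5: half of these, about 0.7, 1.6 and 2.5.
- f = 1: zero.
- f = 1.25: −0.25 times the f = 0 values, so about 0.3, 0.8 and 1.2 toward itopride.

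Both settings show the same pattern: the sign depends on when patients leave, and early leaving can produce a shift comparable with 3.0 points.

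**The case against.** A reader might infer that LOCF is the trial's missing-data method and that it will bias the itopride comparison toward acupuncture. The article supports neither inference.

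- **LOCF is not alone.** It is paired with multiple imputation, a comparison of the two is promised, and mixed models are planned. This stands. It does not settle which result is primary, or whether the mixed model is run on LOCF-filled data.
- **The direction is not fixed.** The article gives no timing of drop-out and no symptom course. The shift is nil if the full improvement had been reached and reverses if patients leave at a peak. Two of the four post-baseline visits fall after treatment. If symptoms return by then, carrying the week-4 score forward overstates benefit most in the arm with more drop-out, which favours itopride. This stands, and the point must be worded as conditional.
- **High drop-out is a possibility with a countermeasure.** The Discussion says it may occur, though its next sentence calls it expected. Free sessions are offered, and the Study design section says patients are told in advance that they may get itopride. These may shrink the imbalance; by how much cannot be known from the article.
- **Selective choice of method is limited.** The statistician is to be blinded to group, and groups are coded by letter. This weakens the worry about picking the favourable result without removing it.
- **Some detail belongs in an analysis plan.** The covariates of the imputation model and the exact form of a tipping-point analysis may be left there. Their absence is no fault here. Removing LOCF altogether would be a preference.

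**Conclusion.** The concern holds in conditional form. The plan gives LOCF equal standing with multiple imputation and names no primary method, while expecting drop-out to be concentrated in an unblinded comparator arm. For early drop-out driven by disappointment with the allocation, which fits the reason the Discussion gives, LOCF favours acupuncture.

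With 20–30% drop-out on itopride against 10% on acupuncture and 18.0 points of true improvement in both arms, the shift runs from 3.6 points toward acupuncture, through zero, to 0.9 toward itopride. Shifts of 3.0 or more arise only near the extreme where patients leave with no improvement at all. The rates, the timing and the equal f in both arms are assumptions.

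The point bears on the itopride comparison, one of three hypotheses. The non-inferiority aim is itself stated only as something to be attempted. The change is worth making because it is cheap and the possible shift is of the same order as the difference the trial regards as important.

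**What to change.** State one primary analysis: the mixed model already planned, fitted to all observed visits with no LOCF-filled values. It is valid if missingness depends only on observed data. Keeping baseline among the modelled visits, as the article's span from baseline to 3 months suggests, lets patients with only a baseline score stay in the analysis, in line with intention to treat.

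Give multiple imputation as the supporting analysis. Keep LOCF, if at all, as a sensitivity analysis labelled as such.

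Preferably, add for the itopride comparison a sensitivity analysis in which the assumed outcomes of drop-outs are varied separately in the itopride and acupuncture arms. Comparing LOCF with multiple imputation does not explore that. Its details can sit in the statistical analysis plan.

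The cost is a few sentences of analysis wording and some programming. No new data, visits or patients are needed.

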### Outcome measurements

Patients will be required to complete the Chinese version of the Nepean Dyspepsia Index (NDI), which has been translated according to the validated long version of the Nepean Dyspepsia Index (NDI) [25]. The reliability and validity of this index were tested in the first phase of the ***973 program***. Patients will also be asked to complete the Symptom Index of Dyspepsia and the Mos 36-item Short Form Health Survey (SF-36). The Symptom Index of Dyspepsia focuses on four symptoms, namely postprandial distension, early satiety, epigastric pain and heartburn. Each symptom is then graded as asymptomatic (0 point), mild (1 point), moderate (2 points) or severe (3 points). The SF-36 is a Chinese version of an English test [2] to assess the quality of life.

The main outcome measurements in this trial will include differences in the Nepean Dyspepsia Index (NDI) and the Symptom Index of Dyspepsia, as measured before randomization, 2 weeks and 4 weeks after randomization, and 1 month and 3 months after the completion of treatment. Secondary outcome measures will include differences in the SF-36 before randomization, 4 weeks after randomization, and 1 month and 3 months after completing treatment.

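### The mixed model names site but no baseline adjustment, leaves the treatment contrast open with baseline among the analysed visits, and lets skew move NDI off its point scale

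*Protocol article*

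**What the plan says.** All of the relevant wording is in the protocol article, mostly under Statistical analysis.

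- **Model.** "General linear mixed models, adjusted for clinical site, will be used to study the effects of treatments on outcomes from baseline to 3 months". Baseline NDI, SID or SF-36 is not named as a covariate anywhere in the article.
- **Visits.** The repeated measures analysis is illustrated by "comparing NDI scores before randomization, 2 weeks and 4 weeks after randomization, and 1 month and 3 months after the completion of treatment". That is five time points, one before treatment and four after baseline.
- **Outcome.** Under Outcome measurements: "The main outcome measurements in this trial will include differences in the Nepean Dyspepsia Index (NDI) and the Symptom Index of Dyspepsia", over the same five visits.
- **Distribution.** "Data distribution is expected to be normal owing to the large sample size". The next sentence says that "any skewed distribution data will be transformed prior to analysis". It names no transformation and does not say how results would return to NDI points.
- **Planning scale.** "an improvement of 3.0 in the NDI scores of two groups will be considered minimally significant", with a standard deviation of 22.0. Both are in raw NDI points.

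The section does not say whether treatment is judged by a group main effect or by a group-by-time contrast. It also does not say whether baseline means are held equal across arms.

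**The concern.** Three features of the stated method could be improved.

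First, a patient's own baseline score is usually one of the strongest predictors of the later score, and every patient has one. A model that names site and not baseline gives that information away, unless it recovers it by constraining the arms to a common baseline mean.

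Second, with baseline in the response and the contrast unstated, different readings of the same sentence give different estimates and different standard errors.

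Third, the normality sentence is wrong as statistics: a large sample makes the sampling distribution of a mean approximately normal and does nothing to the shape of the data. The rule that follows from it is triggered by the data and makes no exception for the primary outcome. If it were applied to NDI, the main contrast might no longer be in the points in which the 3.0 difference and the SD of 22.0 are set.

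**Working it through.** **Inputs from the article:** difference 3.0, SD 22.0, two-sided 5% significance, 90% power, 120 per group, 15% withdrawal (120 × 0.85 = 102 completers per arm), five visits. **Assumed:** baseline-to-follow-up correlation r = 0.3, 0.5 or 0.7, and equal SD at each visit. The article gives no correlation and does not say whether 22.0 is the SD of a score or of a change.

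**The plan's own figure.** n = 2 × [22 × (1.960 + 1.282) / 3]² = 1131 per group, not 120. The stated 120 does follow from a difference of 10 points (n = 102; 102 / 0.85 = 120). This is a separate problem. It is noted because it sets the level of precision against which the rest is read.

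**Detectable difference at 90% power, unadjusted.** 22 × 3.242 × √(2/n) = 9.21 points at n = 120 and 9.99 at n = 102.

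**Gain from baseline adjustment at one visit.** With σ² the variance of a score, the variances are proportional to:

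- follow-up score: 1
- change score: 2(1 − r)
- baseline-adjusted score: 1 − r²

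The adjusted-to-change ratio is therefore (1 + r)/2, and the adjusted-to-follow-up ratio is 1 − r². The detectable differences below are 9.99 times the square root of the ratio.

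| r | ratio to change score | ratio to follow-up score | detectable, n = 102, if 22 is SD of change | detectable, n = 102, if 22 is SD of score |
|---|---|---|---|---|
| 0.3 | 0.65 | 0.91 | 8.05 | 9.53 |
| 0.5 | 0.75 | 0.75 | 8.65 | 8.65 |
| 0.7 | 0.85 | 0.51 | 9.21 | 7.13 |

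At r = 0.5 the two readings of the SD coincide. With 120 per arm the fall is from 9.21 to 9.21 × √0.75 = 7.97.

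**What the open contrast can mean.** Take a constant 3.0-point effect at all four post-baseline visits, SD 22, compound symmetry (assumed) and 102 per arm.

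| Contrast | estimates | SE at r = 0.3 / 0.5 / 0.7 | power |
|---|---|---|---|
| Group main effect over five visits, baseline unconstrained | 4/5 × 3.0 = 2.4 | 2.04 / 2.39 / 2.69 | 22% / 17% / 14% |
| Post-baseline mean minus baseline (group-by-time) | 3.0 | 2.88 / 2.44 / 1.89 | 18% / 23% / 36% |
| Post-baseline mean, baseline-adjusted | 3.0 | 1.91 / 1.89 / 1.65 | 35% / 36% / 45% |

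Only the first row is diluted, by 20%. The second keeps the full effect but has a larger standard error than the third at every r shown.

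**Does adjustment rescue the sample size?** No. At a single visit, with 22 as the SD of a score and r = 0.7, 1131 × 0.51 gives about 577 per group for 3.0 points.

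**Scale.** The difference and the SD are raw points, while the transformation rule covers any skewed data. A contrast on a log scale, for example, is a ratio and does not correspond to a fixed 3.0-point difference. Back-transformation does not in general recover a difference in mean points.

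**The case against.** The strongest reply is that this is a condensed article. The covariate list, covariance structure and exact contrast are commonly left to a full protocol or analysis plan, neither of which is shown, and the text says adjusted for site, not adjusted only for site. That stands as far as silence goes: the absence of a baseline covariate is not proof that none will be used. What remains is the method the article does state. It names one adjustment, lists baseline among the analysed visits, gives a wrong reason for expecting normality, and sets a transformation rule.

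Two stronger readings are tempting, and the article supports neither.

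- *The plan dilutes the treatment effect by 20%.* This needs the test to be a group main effect over all five visits with baseline unconstrained, and the article never says so. Outcomes defined as differences across visits fit a change or group-by-time contrast at least as well, and that contrast is not diluted. Keeping baseline as a response is not an error in itself: with a common baseline mean across arms it is about as efficient as covariate adjustment.
- *The main result will not be in NDI points.* This would follow only if NDI proved skewed, were transformed, and were not reported on the original scale. The article makes this possible and does not state it.

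It is also fair to say that the size of the precision gain rests on assumed correlations and that the article does not name a change score as its estimator. For that reason both comparators are shown.

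**Conclusion.** The point holds as a worthwhile improvement to the stated analysis; it does not show that the analysis is invalid. At every correlation examined, baseline adjustment is more precise than an unadjusted change score (variance × 0.65 to 0.85 for r from 0.3 to 0.7) and than an unadjusted follow-up score (× 0.91 to 0.51). At r = 0.5 the saving is about 1.3 NDI points in the detectable difference at 102 completers per arm. These sizes depend on the assumed correlations and on equal variances over time. The 20% shrinkage is conditional on a test that the article does not specify. The normality statement is wrong whatever the data show, and the transformation rule conflicts with a planning difference fixed in raw points if it is ever triggered for NDI. None of this makes 120 per group adequate for 3.0 points.

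**What to change.** Amend the analysis wording before unblinding.

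1. Model the post-baseline NDI, SID and SF-36 values with the baseline value of the same measure and clinical site as covariates. Alternatively, keep baseline as a response with one common baseline mean across arms.
2. State that inference rests on post-baseline arm contrasts and not on a main effect that includes the baseline visit.
3. Delete the claim that a large sample makes the data normal. Report untransformed NDI as the main estimate, with robust or bootstrap intervals as the check for skew.

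The cost is wording only: Table 1 already schedules all three measures at week 0 and at the later visits. The choice of primary time point, the covariance structure and any ordinal check for SID can stay in the analysis plan, and the sample size needs its own correction.
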